## Participant Exclusion Criteria

Any potential participants meeting any of the following criteria will be excluded from the study:

• Personal or family history of post-streptococcal disease (rheumatic fever or glomerulonephritis), or collagen-vascular disease;

• Has evidence of increased cardiovascular disease risk (defined as >10%, 5 year risk) as determined by the method of Gaziano et al., (36). Risk factors include sex, age, systolic blood pressure (mm Hg), smoking status, body mass index (BMI, kg/m2), reported diabetes status and blood pressure;

• Clinical diagnosis or evidence of recent group A streptococcal infection as measured by anti-streptolysin O or anti-DNase B levels exceeding 200 units;

• Positive group A streptococcus throat culture at screening visit or positive rapid antigen test result on day of study product administration;

• Evidence of multiple past group A streptococcus infections as measured by anti-J8 antibodies levels > 3 Standard Deviations above background Optical Density;

• Presence of significant acute infections requiring systemic antibiotic treatment within the 14 days prior to each product administration;

• Pregnant or breast feeding (all women will have a negative pregnancy test result prior to each study product administered);

• Immunized or intent to immunize with any vaccine or investigational agents within 30 days prior to enrollment through to 30 days following the last study vaccine administration, with the exception of licensed inactivated influenza vaccines;

• Receipt of diphtheria toxoid containing vaccine within the previous 5 years (such as DTP, Hepatitis A, Boostrix, Adacel or Menactra);

• Past significant reaction following any previous vaccination;

• History of hypersensitivity to any diphtheria toxoid containing vaccine;

• Presence of acute infectious disease or fever (e.g., sub-lingual temperature  38.5°C) within the five days prior to study product administration;

• Presence of current or suspected serious chronic diseases such as cardiac or autoimmune disease (HIV or other immunodeficiencies), insulin dependent diabetes, progressive neurological disease, severe malnutrition, acute or progressive hepatic disease, acute or progressive renal disease, psoriasis, rheumatoid arthritis, asthma, epilepsy or obsessive compulsive disorder, skin carcinoma excluding non spreadable skin cancers such as basal cell and squamous cell carcinoma;

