### Handling of Withdrawals

If the participant is withdrawn from the study procedures or follow-up for any reason, with the participant’s permission, medical care will be provided for any SAEs that might have had occurred during the individual participation in the study until the symptoms of any SAEs are resolved and the participant’s condition becomes stable. If withdrawal from further product administration occurs, if willing the participant will be asked to continue the scheduled evaluations and to complete the early termination evaluation as described in section 7.6.

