## Concomitant Medications/Treatments

Concomitant medications/treatments will be recorded during the 0-7 days following each dose and at the scheduled study visits (see Appendix A) and collected surrounding adverse events/serious adverse events. This documentation will include any prescription or nonprescription drug or other treatment. The name of the medication, start and stop dates of treatment, total daily dose, route of administration and indication will be recorded on the source documents.

Permitted concomitant medications:

- These medications include licensed hormonal contraceptives, antihistamines and decongestants for seasonal allergies, non-steroidal anti-inflammatory drugs, (e.g., ibuprofen), non-narcotic analgesics (e.g., paracetamol/acetaminophen) and antibiotics as medically indicated.

At each of the scheduled visits circumstances that could potentially interfere with the vaccine-induced immunity will also be checked for. These circumstances include:

1. Use of any investigational drug or investigational vaccine other than the study vaccine during the study period.

2. Administration of licensed vaccines within 30 days prior to screening and enrollment through to 30 days following the last study vaccine administration, with the exception of licensed inactivated influenza vaccines.

3. Administration of immunosuppressants or other immune-modifying drugs (as listed in the exclusion criteria)

4. Administration of immunoglobulins and/or any blood products up to 28 days after the last dose of vaccine.

5. Antibiotics prescribed for streptococcal throat infection.

If any of the participants require medications/treatments that are listed as exclusion criteria, the participant will be excluded from receiving further doses of the vaccine and will not be included in the immunogenicity evaluations. However, the participant will be encouraged to continue the scheduled follow-up visits and remain in the study for safety evaluation for doses already received.

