**Day 56 ± 5 (Day of Dose 2)**

1. Ensure that an approval has been granted from SMC to proceed with the second study product administration.

2. Review inclusion/exclusion criteria.

3. Review medical history for any change in status from last study visit.

4. Review any acute complaints/adverse events/serious adverse events.

5. Review concomitant medications. If the participant has received an antibiotic treatment within 14 days prior to this administration, at discretion of the CI the participant may be withdrawn from the study or the administration of the second dose rescheduled within the allowed window for administration of the dose.

6. Record baseline symptoms and vital signs. If the participant is febrile (temperature >38°C [>100.4F] or has an acute illness, the study product administration must be rescheduled within the allowed window for administration of the dose.

7. Obtain a throat swab and conduct a rapid antigen test for group A streptococci.

8. Obtain a urine sample from all female participants for -HCG testing. Ensure that the testing is negative before study product administration.

9. Perform breath alcohol test and urine drug screen.

10. Collect urine for urinalysis and blood for hematology, biochemistry and serology including, ASOT, α-DNase B and detection of α-J8 peptide vaccine specific antibodies and blood sample for quantitative cellular response as well as serum samples for α-DT antibodies and safety serum storage (refer to appendix D for tests required and blood volumes).

11. Targeted physical examination including cardiac auscultation. Particular attention to any elicited symptoms and signs consistent with rheumatic fever i.e. rash, arthalgia/arthritis (joint pain/swelling), renal angle tenderness and cardiovascular examination and movement disorder.

12. Administer the study product in the alternate arm from previous dose.

13. Observe for at least 30 minutes after study product administration to evaluate for immediate adverse reactions. Repeat vital signs after approximately of 30 minutes after study product administration, or at least prior to discharge. Record any immediate injection site reaction or systemic reactions if they occur.

14. Educate the participant during the post-study product administration waiting period on proper use of the thermometers and injection site reaction measurement aid. Discuss the signs and symptoms of potential adverse events (AEs).

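### The Day 56 rules for deferring Dose 2 do not agree with the exclusion look-backs, or with the sections that keep participants in safety follow-up after they stop product

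*Protocol*

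**What the plan says.** Protocol section 7.3 sets the Dose 2 visit at Day 56 ± 5, and the schedule in the Protocol Summary gives the same window. Three steps of that visit matter here.

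- Step 2 has the site review the inclusion and exclusion criteria again.
- Step 5 opens with "If the participant has received an antibiotic treatment within 14 days prior to this administration". At the clinical investigator's discretion, it then offers two courses: "the participant may be withdrawn from the study or the administration of the second dose rescheduled within the allowed window for administration of the dose".
- Step 6 covers a participant with a temperature above 38°C or an acute illness. Moving the dose inside the same window is mandatory, and no other course is named.

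Two of the exclusion criteria in section 5.2 act on the same visit. One is "Presence of significant acute infections requiring systemic antibiotic treatment within the 14 days prior to each product administration". The other concerns acute infectious disease or fever, with 38.5°C as its example temperature, "within the five days prior to study product administration".

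Two other sections say what happens to someone who stops product. Section 5.3.5 (Handling of Withdrawals) says that "if willing the participant will be asked to continue the scheduled evaluations". Section 6.4 (Concomitant Medications/Treatments) covers a participant who needs a treatment listed as an exclusion criterion. That person gets no further doses and leaves the immunogenicity evaluations, but "the participant will be encouraged to continue the scheduled follow-up visits and remain in the study for safety evaluation for doses already received". Section 6.4 also lists medically indicated antibiotics among the permitted medications.

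**The concern.** There are two inconsistencies.

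The first is one of timing. A site that defers Dose 2 because of a look-back has at most five days left from the nominal visit, while one of the look-backs is 14 days and the other is five. For many participants no day satisfies both the window and the exclusion criterion. Step 6 orders rescheduling within the window and does not say what follows when that is impossible. The triggers also differ. Step 5 reacts to any antibiotic, but section 5.2 only to a significant infection needing a systemic one. Step 6 reacts above 38°C, while section 5.2 cites 38.5°C.

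The second matters more. Step 5 allows removal from the study, not just from product, because of a recent antibiotic. Safety is the primary objective. The remaining visits (Days 84, 180, 266 and 350) carry the laboratory tests and cardiac auscultation, with ECG and ECHO on Days 84 and 350. These assessments address the cardiac and autoimmune risk described in section 2.3.1. Reserve participants step in only before the first injection (section 5), so a participant lost at Dose 2 is not replaced.

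**Working it through.** The protocol gives no figure of its own on this point, so there is nothing to reproduce. The check counts calendar days.

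**Inputs**
- Dose 2 window: 56 ± 5, so Days 51 to 61 (section 7.3; Protocol Summary).
- Look-backs: 14 days and five days (section 5.2).
- Safety Monitoring Committee review of Dose 1: Day 49 ± 5 (Protocol Summary), at least seven days before the next injection (section 11.4).
- Active arm: 15.

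**Antibiotic look-back**

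Let P be the day the participant presents and d the last antibiotic day before P. The count applies only where the antibiotic treated a significant infection of the kind in section 5.2, and it dates the look-back from d. The protocol does not say whether a gap of exactly 14 days is inside the look-back, so both readings are shown.

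- Strict (14 days is inside): the rule triggers if P − d ≤ 14, and Day 61 is compliant only if 61 − d > 14, so d ≤ 46. For P = 56 the triggering days are 42 to 55 (14 days). Days 47 to 55 (9 days) leave no compliant date: 9/14 = 64%.
- Lenient (14 days is clear): the rule triggers if P − d < 14, and Day 61 is compliant if d ≤ 47. For P = 56 the triggering days are 43 to 55 (13 days). Days 48 to 55 (8 days) leave no compliant date: 8/13 = 62%.

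For any P in the window the shares are (P − 47)/14 strict and (P − 48)/13 lenient:

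| Presents on | Strict | Lenient |
| --- | --- | --- |
| Day 51 | 4/14 (29%) | 3/13 (23%) |
| Day 54 | 7/14 (50%) | 6/13 (46%) |
| Day 56 | 9/14 (64%) | 8/13 (62%) |
| Day 58 | 11/14 (79%) | 10/13 (77%) |
| Day 61 | 14/14 (100%) | 13/13 (100%) |

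Counting an antibiotic taken on the visit day itself adds one to numerator and denominator. At Day 56 that gives 10/15 (67%) strict and 9/14 (64%) lenient.

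**Committee gap**

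Earliest Dose 2 = review day + 7. A review on Day 44 gives Day 51, on Day 49 gives Day 56, and on Day 54 gives Day 61. The rows before Day 56 are therefore open only if the committee meets before Day 49.

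**Five-day look-back**

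Let e be the last day of infection or fever. The earliest compliant day is e + 6 (strict) or e + 5 (lenient).

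- e = 56: Day 62 or Day 61. At most one day remains, the last of the window.
- e = 57: Day 63 or Day 62. None remains on either count.
- Presenting on Day 51: the illness may last until Day 55 (strict) or Day 56 (lenient), so four or five further ill days still fit.

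**Withdrawal**

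Section 5.3.5 separates two cases. After withdrawal from product, a willing participant continues the scheduled evaluations. After withdrawal from study procedures or follow-up, the only provision is medical care for serious adverse events. Step 5 uses the wording of the second case for a situation that sections 5.3.5 and 6.4 otherwise handle as the first. One vaccine recipient is 1/15 = 6.7% of the active arm.

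**The case against.** The strongest reply is that the protocol can be operated as written. Step 5 is discretionary and offers an alternative to deferral. Deferral from Day 56 works when the last antibiotic day was Day 46 or 47 or earlier, and for more timings at earlier presentation. Section 5.3.4 lets the investigator stop product for an illness or other situation, and section 6.4 gives a route with no further doses. A missed Dose 2 is therefore largely foreseen. This stands: a reader might infer that the deferral rule cannot be followed at all, or that a site is driven to dose against an exclusion criterion. The documents support neither. No passage directs dosing in breach, and step 2 re-checks eligibility first.

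The reply also notes that the triggers differ, so not every antibiotic day or raised temperature under steps 5 and 6 engages section 5.2. That stands too, and it is why the shares above are conditional. It is also a further inconsistency to reconcile.

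On withdrawal, the reply is that step 5 is loose wording and section 5.3.5 supplies the missing handling. The early termination visit in section 7.6 includes auscultation, ECG, ECHO and laboratory tests. This softens the point without removing it. Section 7.6 offers that visit after voluntary withdrawal. It is a single voluntary evaluation, and does not replace the schedule to Day 350.

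Finally, the trial is descriptive, with no formal testing (section 11.6), so one lost second dose upsets no planned inference. That is right, and it limits the weight of the timing point.

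**Conclusion.** The point holds as an inconsistency between the Day 56 instructions and sections 5.2, 5.3.5 and 6.4.

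On timing, about 62–64% of antibiotic timings have no compliant date from nominal Day 56. The share is lower for earlier presentation and higher for later. It rests on three assumptions: equally likely timings, an antibiotic given for a significant infection, and a look-back dated from the last antibiotic day. It is not an expected rate of missed doses, because the protocol gives no frequency of antibiotic use or fever. For fever, a reader might infer that deferral usually fails. That is not established: for an illness that ends on the day of presentation, no date fits on 5 or 6 of the 11 window days (lenient or strict). The firm part is that step 6 is mandatory and silent once the illness outlasts the window.

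On withdrawal, the conflict does not depend on any of this counting. A site that follows step 5 literally could lose the Day 84 to Day 350 safety data on a participant whom other sections would keep in follow-up. Appendix A, which also holds visit windows, is not available here; the ± 5 days rests on section 7.3 and the Protocol Summary, which agree.

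**What to change.** Reconcile section 5.2 with steps 5 and 6 of the Day 56 visit, so that the triggers, look-back intervals and Dose 2 window agree. Say whether the boundary day counts as inside a look-back, and state the outcome when a look-back outlasts the window. Reconcile step 5 with sections 5.3.5 and 6.4 on whether withdrawn means from further product or from the study, so that safety follow-up is handled the same way throughout. Which interval, window or clinical rule applies is for the sponsor to decide.

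The cost is a wording amendment. Depending on the sponsor's choice, it brings either a somewhat wider spread of dose intervals or an explicitly accepted missed Dose 2.

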**Day 58± 1 (2 days after Dose 2, telephone call)**

1. Enquire for any acute complaints/adverse events/serious adverse events.

2. Review MA for solicited local and systemic reactogenicity and unsolicited events

3. Review concomitant medications.

**Day 64 + 2 (8 days after Dose 2, telephone call)**

1. Enquire for any acute complaints/adverse events/serious adverse events.

2. Review MA for solicited local and systemic reactogenicity and unsolicited events

3. Review concomitant medications.

**Day 84 ± 7 (28 days after Dose 2)**

1. Review medical history for any change in status from last study visit

2. Review any acute complaints/adverse events/serious adverse events.

3. Review concomitant medications.

4. Record vital signs.

5. Collect urine for urinalysis and blood for hematology, biochemistry and serology including ASOT, α-DNAse B, detection of α-J8 peptide specific antibodies and quantitative cellular response.

6. Targeted physical examination including cardiac auscultation. Particular attention to any elicited symptoms and signs consistent with rheumatic fever i.e. rash, arthalgia/arthritis (joint pain/swelling), renal angle tenderness and cardiovascular examination and movement disorder

7. Perform ECG and ECHO.

## Follow-up

See Appendix A for a tabular presentation of study procedures at these visits.

**Day 180 ± 14 (approximately 17 weeks after the last injection)**

1. Review medical history for any change in status from last study visit

2. Review any acute complaints/adverse events/serious adverse events.

3. Review concomitant medications.

4. Record vital signs.

5. Targeted physical examination including cardiac auscultation, paying particular attention to any elicited symptoms and signs consistent with rheumatic fever (rash, arthalgia/arthritis, renal angle tenderness abnormal cardiovascular findings or movement disorder.

6. Collect blood for hematology, biochemistry and serology including ASOT, α-DNAase B, and detection of α-J8 peptide vaccine specific antibodies and quantative cellular response. Collect urine for urinalysis.

**Day 266 ± 14 (approximately 30 weeks after the last injection)**

1. Review medical history for any change in status from last study visit

2. Review any acute complaints/adverse events/serious adverse events.

3. Review concomitant medications.

4. Record vital signs.

5. Targeted physical examination including cardiac auscultation, paying particular attention to any elicited symptoms and signs consistent with rheumatic fever (rash, arthalgia/arthritis, renal angle tenderness abnormal cardiovascular findings or movement disorder.

6. Collect blood for hematology, biochemistry and serology including ASOT, α-DNAase B, and detection of α-J8 peptide vaccine specific antibodies and quantative cellular response. Collect urine for urinalysis.

## Final Study Visit

See Appendix A for a tabular presentation of study procedures at these visits.

**Day 350 ± 14 (approximately 42 weeks after the last injection)**

1. Review medical history for any change in status from last study visit

2. Review any acute complaints/adverse events/serious adverse events

3. Review concomitant medications.

4. Record vital signs.

5. Targeted physical examination including cardiac auscultation by a physician. Paying particular attention to any elicited symptoms and signs consistent with rheumatic fever (rash, arthalgia/arthritis, renal angle tenderness and abnormal cardiovascular findings or movement disorder).

6. Collect blood for hematology, biochemistry and serology including ASOT and α-DNAse B, detection of α-J8 peptide vaccine specific antibodies, blood sample for quantitative cellular response as well as serum samples for α-DT antibodies and safety serum storage (refer to appendix D for tests required and blood volumes). Collect urine for urinalysis.

7. Perform ECG and ECHO.

If a participant’s ECHO is abnormal on the last scheduled visit, evaluations will continue until the ECHO results are read as normal or the condition has stabilized.

At the completion of the study, a letter will be forwarded to all participants’ general practitioners (GP) to inform them of:

• The participation of their patients in this study and the type of vaccine that they have received.

• The titer of the antibody response to the vaccine antigen, including the anti diphtheria toxoid antibodies measured at the final study visit with recommendation for any further administration of diphtheria toxoid containing vaccines.

• Any ongoing associated and not associated AE

## Early Termination Visit

Each participant may withdraw voluntarily at any stage of the study for any reason. Participants who withdraw from receiving further study product will however be encouraged to continue follow up visits as per schedule for the purpose of monitoring for safety outcomes.

If voluntary withdrawal occurs at any stage of the study, and the participant does not wish to continue the follow up visits the participant will be asked to complete an end-of-study evaluation. Participation in an end-of-study evaluation by each participant is voluntary. Activities during early termination visit will include:

• Review of Concomitant Medications

• General physical examination, including the injection site examination, will be performed;

• Review of memory aid at the termination visit if it has not been done previously;

• A cardiac evaluation by cardiac auscultation, electrocardiogram and transthoracic echocardiogram

• Blood samples will be taken for hematology and serum/biochemistries analyses, serum for safety serum storage and antibody for ASOT, α-DNAse B, and ELISA for J8 and D vaccine specific antibodies; Urine samples will also be collected for urinalysis by dipstick.

• In a case of occurrence of serious adverse events, regardless of whether or not it is judged to be vaccine related, the participant will receive appropriate care under clinical supervision until all the symptoms of the serious adverse events have diminished or resolved and the participant’s condition improved.

For ongoing AEs care will be provided for a period of time as specified in the clinical site work instruction protocols. However, if the nature of the ongoing adverse event is determined by the CI not being vaccine associated the participant will be advised to visit his/her own GP for further clinical care that he/she might require.

## Unscheduled Visit

In the event that a participant has an unscheduled visit, the visit will be documented. Data collected would include information appropriate to the situation, such as event history, a limited physical examination and/or laboratory tests.

# Study Procedures/Evaluations

## Clinical Evaluations

Active surveillance by clinical personnel will be undertaken for each participant at enrollment prior to administration of the first injection and at all clinic visits.

• Clinical personnel involved in this study will interview each participant at screening to collect information regarding the medical history of all the participants. At screening, this will include demographic information, age and ethnic origin, personal and family history of all known diseases or conditions, especially those listed in the exclusion criteria. Information will also be collected whether the participant had received vaccination with a diphtheria toxoid containing vaccine within the previous 5 years (Diphtheria toxoid, tetanus toxoid, acellular pertussis vaccines, diphtheria toxoid and tetanus toxoid vaccines, pneumococcal conjugate vaccine, Menactra) as this vaccination is an exclusion criterion for participation in the study. Medical history will be reviewed prior to administration of each vaccine dose and at every clinic visit (see Appendix A).

• A medication history will also be collected at screening, during all study visits and surrounding any adverse/serious adverse events. It will include all medications that are currently taken by all participants regardless of whether they are prescription medications for treatment of persistent condition such as antidepressants, antibiotics, contraceptive medications (for females), other vaccines or over-the-counter medications.

• Vital signs will be collected and acute complaints examined by clinical personnel prior to each study product administration and at all scheduled clinic visits. Each participant will be subject to a physical examination by a physician at screening to evaluate the general health status of the participant. This will include body weight, vital signs (blood pressure, temperature, heart rate and respiratory rate), an examination of vital organs and cardiac auscultation. Targeted (abbreviated) physical examination including cardiac auscultation will also be performed prior to study product administration of each injection and at all scheduled study visits (Appendix A). Exam will include particular attention to any elicited symptoms and signs consistent with any adverse events. Any deviations from normal will be reported to the study physician for a review. All deviations from normal detected by physical examination will be graded as 1 (mild), 2 (moderate), 3 (severe) and 4 (life threatening) (see Appendix B).

• Transthoracic echocardiography (ECHO) and electrocardiogram (ECG) tests will be performed for each participant in this study at screening, 28 days after each injection and at the final visit on day 350 by a technician blinded to the type of treatment that the participants are receiving. A single echo technician and a single cardiologist have been recruited to perform and interpret all ECHO findings. The technician will be located at the clinical site and the cardiologist reading the findings will be located in the hospital which is physically separated from the clinical site where study activities will be conducted. There will be no discussion regarding the clinical trial between the trial personnel and the hospital personnel. Echocardiograms will be reviewed for any abnormalities by the study cardiologist who will be also blinded to type of treatment that the participants are receiving. If any findings are identified as abnormal a second cardiologist will be asked to independently review the test results and report on the findings. If an abnormal ECHO/ECG is confirmed, it will be reported to the Independent Safety Monitor and Safety Monitoring Committee to determine whether it meets halting rules. Any change in degree of mitral regurgitation with EROA 10-19mm2 but a change of <10mm2 from baseline will be followed on a monthly basis with echocardiogram on a monthly basis until stable (Appendix H).

• The injection site will be examined immediately before and after each dose. The reactogenicity of the study product will be determined by assessing the local pain, tenderness and pruritis and measuring the erythema/redness and induration/swelling at the injection site using the injection site reaction measurement tool (Appendix C).

• Solicited systemic symptoms (see section 9.2.1) will be assessed prior to study product administration and at 30 minutes after each dose. Memory aids will be given to each participant on each product administration day. All participants will be asked to record the occurrence of any injection site reaction or general symptoms for 7 days following each dose in memory aids as indicated in section 9.2.1. A telephone call will be made by a study nurse to each participant at 2 days and 8 days after each injection. All participants will be encouraged to call the clinical personnel involved in this study on the provided contact details, or to visit the clinical site if they observe any reactions, grade 3 or above as specified in this protocol (see Appendix B), or if they have any concern. Any AE that occurs greater than 7 days after each dose should be reported to the clinical study personnel during the scheduled interim visits or by calling the designated contact person. All AEs will be assessed during each study visit.

